**Figure 1 F1:**
[figure not shown]
**Study Design**.

The management boards of the four participating nursing home associations agreed with the implementation of the EXBELT program. After allocation of the wards to intervention and control groups, written information about the study will be given to the residents' legal representatives, and written informed consent will be obtained from the legal representatives of the nursing home residents in order to include those residents in the study. Data will be collected at baseline (T1), and four (T2) and eight (T3) months after baseline.

The study design and protocol were approved by the Medical Ethics Committee of the University Hospital Maastricht and Maastricht University. In addition, local Ethical Committees of participating institutions have given their consent to the protocol and procedures.

### Sample size considerations

Sample size calculations are based on the primary outcome measure for residents: proportion of residents using a belt. We expect a reduction of 50% in belt use in the intervention group and no changes in use in the control group. Based on a significance level α of 0.05 (two sided) and a power of 60%, 216 residents are needed in each group in the analyses. Taken into account an informed consent rate of 80% and a drop-out rate of 25%, 720 psychogeriatric nursing home residents have to be selected at the start of the study.

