## Background

The use of physical restraints still is common practice in the nursing home care of older people with dementia. Physical restraints are defined as any limitation in an individual's freedom of movement [1] and includes those worn by the person (belt, chest, and arm/leg), those attached to beds (full-enclosure bedrails) or chairs (locked table). Although reports of restraint prevalence internationally varies from 15 to 66% [2,3], ranges of restraint prevalence in Dutch nursing homes is between 41 to 64% [2]. Recent prevalence measures in the Netherlands have shown that 10% to 14% of nursing home residents are restrained with belts [4,5].

Staff report that physical restraints are used to prevent falls [6-8]. The accumulating evidence that restraint reduction does not lead to an increased number of falls or fall-related injuries [9-11] and that restraint use can result in falls and problems with balance and coordination [6,12,13], call into question the continued use of these devices as "safety measures". Restraints have other known negative physical, psychological and social consequences for older persons. Both prolonged and short periods of physical restraint use are associated with pressure sores, loss of muscle strength and endurance, joint contractures, incontinence, demoralization, humiliation feelings of low self worth, depression, aggression and impaired social functioning [6,14,15]. Evans and colleagues [12] conducted a systematic review of physical restraint use in acute and residential health care facilities, and documented that the use of physical restraints (including belts), increases the risk of death, serious injury, as well as the length of hospital stay. Older adults report negative feelings about the restraint experience such as discomfort and indifference [16]. The use of restraints may also indicate a failure to address the real needs of the residents. Since physical restraints have been shown to be an ineffective and sometimes even hazardous measure, interventions are needed to reduce their usage.

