## Methods/Design

### Design and sample

Effects of EXBELT will be studied in a quasi-experimental longitudinal study design. Alongside the effect evaluation, a process evaluation will be carried out in order to further develop EXBELT. Figure 1 shows the design of the study presented. After contacting seven Dutch nursing home associations (networks of nursing homes) in order to assess whether they would be interested to participate in our study, four nursing home associations, located in three regions in the Netherlands (Zuid-Limburg, Midden Limburg/Zuid-Oost Brabant en Zuid-Holland) contacted the EXBELT research group to participate in the current study. To participate, the prevalence of belt use on psychogeriatric nursing home wards had to be at least 10%. Wards are excluded if the unit is dedicated to residents with Korsakoff's, if far-reaching reorganizations and/or constructional renovations will be implemented, and if participating in other studies and/or projects aimed at the reduction of restrain use. The total study sample comprises four nursing home associations, 13 nursing homes with a total of 26 psychogeriatric wards. The 26 wards were assigned to either the intervention or control group. Assignment to either to intervention or control groups was carried out by the research team. Since no randomization took place, allocation was based on avoidance of contamination bias. Overlap of nursing home staff between the intervention and control wards was averted. In addition, based on the geographical location of the participating wards, wards from each of the four nursing associations that were situated closely together were allocated to the same group. The wards allocated to the control group will receive care as usual, while the wards allocated to the intervention group will receive the EXBELT program.

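### The 60% power is stated with no allowance for ward clustering although whole wards are allocated; within the cited belt prevalence, a ward ICC above about 0.01 takes power below 60%

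*Protocol article*

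**What the plan says.** Protocol article, Sample size considerations. The calculation is at resident level: "Sample size calculations are based on the primary outcome measure for residents: proportion of residents using a belt". The effect assumed is "We expect a reduction of 50% in belt use in the intervention group and no changes in use in the control group", at a two-sided 5% level. The result is "a power of 60%, 216 residents are needed in each group in the analyses". The only inflation described is "Taken into account an informed consent rate of 80% and a drop-out rate of 25%, 720 psychogeriatric nursing home residents have to be selected". The section gives no control prevalence, ICC, design effect, ward size or number of wards per group.

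Protocol article, Design and sample. Allocation was not by resident: "The 26 wards were assigned to either the intervention or control group". It was not randomised, and wards of an association that were "situated closely together were allocated to the same group". There are 13 homes and four associations. Belt prevalence of at least 10% was required for entry.

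Protocol article, Background. The only prevalence range cited for belts is "10% to 14% of nursing home residents are restrained with belts", and it refers to Dutch nursing home residents in general.

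**The concern.** EXBELT acts on the ward and the institution: a policy prohibiting belts, staff education and consultation. Whether a resident wears a belt depends partly on the practice of the ward, so residents of one ward are unlikely to be independent observations. When whole wards are allocated, positive within-ward correlation inflates the variance of the group comparison, and a calculation for independent residents then overstates the power.

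The stated power is already low, so there is no margin to absorb this. A non-significant primary result would be judged against a 60% chance of detection that the design may not have, and could be given more weight against EXBELT than it deserves.

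**Working it through.** **Inputs.** From the sample size section: 50% relative reduction, two-sided alpha 0.05, power 60%, 216 per group, 80% consent, 25% drop-out, 720 selected. From Background: belt prevalence 10% to 14%. From Design and sample: 26 wards. Assumed, because the document gives none: ward ICC of 0.01 to 0.10 and equal ward sizes.

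**1. Reproducing 216.** Pooled two-proportion formula for independent residents:

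n = [z(0.975)·√(2·p̄·(1−p̄)) + z(0.60)·√(p1(1−p1) + p2(1−p2))]² / (p1−p2)²

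With p1 = 0.14, p2 = 0.07 and p̄ = 0.105: n = [1.960·√0.18795 + 0.2533·√0.1855]² / 0.0049 = 187.6, so 188.

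Continuity correction: n_cc = (n/4)·[1 + √(1 + 4/(n·|p1−p2|))]² = 215.2, so **216**, the stated figure.

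Other control rates, 60% power:

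| Control vs intervention | Uncorrected n per group | Continuity-corrected n per group |
|---|---|---|
| 10% vs 5% | 272 | 311 |
| 12% vs 6% | 223 | 255 |
| 13% vs 6.5% | 204 | 234 |
| 14% vs 7% | 188 | 216 |

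Without the correction, 60% power at 216 corresponds to a control rate of about 12.3%.

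**2. Reproducing 720.** 2 × 216 = 432, and 432/(0.80 × 0.75) = 720. Consent and drop-out account for the whole step, so it holds no clustering allowance.

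**3. Room for an allowance inside the 216.** Ward size in the analysis is m = 432/26 = 16.6. The largest allowance within the cited range comes from the uncorrected 188 at 14%: 216/188 = 1.149, so ICC = 0.149/15.6 = 0.0095, about 0.01. Above that, 216 per group gives less than 60% anywhere from 10% to 14%.

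**4. Power with ward clustering.** Design effect DE = 1 + (m−1)·ICC; effective n = 216/DE.

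| Assumed ICC | DE | Effective n per group | 14% vs 7%, corrected | 14% vs 7%, uncorrected | 12% vs 6%, uncorrected |
|---|---|---|---|---|---|
| 0 | 1.00 | 216 | 60% | 66% | 59% |
| 0.01 | 1.16 | 187 | 53% | 60% | 53% |
| 0.02 | 1.31 | 165 | 47% | 55% | 48% |
| 0.05 | 1.78 | 121 | 35% | 43% | 37% |
| 0.10 | 2.56 | 84 | 23% | 32% | 27% |

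The corrected column is on the basis that reproduces 216, so it alone shows the fall from exactly the stated 60%. The uncorrected columns start from 66% and 59% and should be read against those values.

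**5. Worst case at the entry floor.** If mean prevalence were only 10%, uncorrected power at 216 per group would be 50.5% with no clustering and 31% at ICC 0.05. The floor is a minimum for entry, so this is a lower bound and not an expected value.

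**The case against.** A reader might infer that the 216 has been shown to contain no design effect. The document does not support that. The control rate and the formula are not stated, so the match in step 1 rests on two choices made here. An uncorrected 14% versus 7% multiplied by 1.156 (ICC 0.01) gives 188 × 1.156 ≈ 217, which fits about as well.

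The planners may also have assumed a prevalence above 14%. The cited range describes nursing home residents generally, while entry required at least 10%, which could raise the mean. The pilot ward had 12 belts among 30 residents, although the article calls that home atypical. At 20% versus 10%, uncorrected power at 216 is 83% without clustering, 72% at ICC 0.02 and 59% at ICC 0.05. This stands as a limit on the conclusion, but the article states no such rate.

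Baseline adjustment is planned (Data analysis) and could recover precision. If adjustment multiplies the variance by 1−r², cancelling the design effect at ICC 0.02 or 0.05 needs r = √(1−1/DE), about 0.49 or 0.66. The document gives no such correlation, and the sample size section claims no gain from adjustment.

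An article may leave the ICC and cluster sizes to the full protocol, and this one openly declares a low power. Both are true. The point, however, concerns a figure that is printed, and for the cited prevalence range that figure needs residents to be independent or nearly so.

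**Conclusion.** The concern holds in a bounded form. The stated 60% names no clustering allowance, reproduces as an independent-resident calculation, and within the cited 10% to 14% leaves room for a ward ICC of at most about 0.01. At assumed ICCs of 0.02, 0.05 and 0.10, power is about 47%, 35% and 23% (14% versus 7%, continuity-corrected), or 48-55%, 37-43% and 27-32% (12% to 14%, uncorrected). The direction is firm for any positive ICC. The size rests on the assumed ICC, the unstated control rate, equal ward sizes and no credit for baseline adjustment.

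It would be tempting to conclude that the trial has well under an even chance of detecting its own target effect. That does not follow in general: at ICC 0.02 power is near even, and a control rate of 20% would give about 59% even at ICC 0.05. Correlation within homes, or among neighbouring wards kept together, would lower power further, but by an amount that the document gives no means to fix.

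**What to change.** Leave enrolment unchanged and rewrite the sample size paragraph to:

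- state the assumed control prevalence and the formula, including whether a continuity correction was used;
- give the number of wards per group, the expected analysed residents per ward, and an ICC range with its justification;
- replace the single 60% with the power at 216 per group over that range, all on one basis;
- show any gain expected from adjusting for baseline belt use as a separate line with its assumed correlation;
- note that correlation within homes is a further, unquantified loss.

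If a design effect was in fact included, or a prevalence above 14% assumed, saying so with the value settles the point.

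The cost is one paragraph and no extra residents. The downside is that the stated power will probably look less favourable.

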### Intervention program

EXBELT is a multi-component intervention that comprises a policy change, in combination with an educational intervention for nursing home staff and consultation by a nurse specialist, and the use and availability of alternative interventions. The four key components of EXBELT are:

1. Implementation of institutional policy change that prohibits belt restraint use including communication of the policy change to:

a. nursing home staff;

b. residents' relatives.

2. Intensive educational intervention program for nursing home staff (nursing home physicians, nurses, paramedical staff, psychologists and ward managers) that address changing staff attitudes. Key parts are:

a. focus on safely reducing belts with the understanding that nursing homes never can guarantee no falls or related injuries;

b. taught by a nurse specialist during three small-scale meetings, each lasting three hours, over a three week period;

c. small-scale meetings attended by nursing home staff from different wards;

d. a 90-minute educational session directed toward all nursing home staff of each intervention ward after the three small-scale meetings were delivered;

e. one specific module focused on strategies for changing attitudes such as shifting perspectives [30,31].

3. Consultation:

a. the nurse specialist who delivered the educational program will provide on-site consultation to individual nurses on the intervention wards regarding challenges in reducing restraints for specific resident cases [18];

b. a nursing home manager and the Netherlands Health Care Inspectorate (IGZ) will be available as a consultant to nursing home managers and clinical staff for individual cases, as needed;

c. representatives of the nursing staffs, product developers, and the research team will discuss problem cases in a creative session.

4. Development and availability of alternative interventions:

a. directors of the involved nursing homes will provide resident centered alternative interventions available including hip protectors, infrared systems, balance training, exercise, special pillows and lower beds;

b. the nurse specialist stimulates en facilitates decision-making regarding alternative interventions by multidisciplinary team;

c. the nurse specialist encourages the use of alternative interventions.

## Measures

### Effect evaluation

The primary outcome measure of the effect evaluation is the use of belts. Belt use will be measured at baseline, T2 and T3 using the observation tool developed by Huizing and colleagues [19,23,24]. Belts per resident will be recorded as present or absent. The use of belts will be measured by a single trained observer, who is blinded to the group assignment, on four times during a 24-hour period (morning, afternoon, evening and night). The day each of the participating wards is visited will be unannounced in order to prevent any artificial removal of belts by nursing home staff.

Secondary outcome measures include other types of physical restraints (e.g. bilateral full-enclosure bedrails, deep or overturned chairs, chairs with a locked tray table, chairs on a board), psychoactive drug use, number of falls and fall-related injuries, the use of alternative interventions, cognitive level, activities of daily living (ADL)-status, ADL-dependency, and mobility. Physical restraint use will be measured at baseline, T2 and T3 using the same observation tool to measure the usage of belts developed by Huizing and colleagues [19,23,24]. Types of physical restraints per resident will be recorded as present or absent. The day each of the participating wards is visited will be unannounced in order to prevent any artificial removal of physical restraints by nursing home staff. Data on psychoactive drug use will be collected at baseline, T2 and T3 using the residents' medical records. Falls and fall-related injuries will be recorded retrospectively (three months preceding each of the three measurements, using the register of falls that Dutch nursing homes are required to maintain [32]. The use of alternative interventions used will be monitored continuously, using a report chart (addressing type of intervention) that will be filled out by the nursing staff. Data concerning cognitive level, activities of daily living (ADL)-status, ADL-dependency, and mobility will be collected only for those residents who are restrained by a belt. Cognitive status will be measured using the Cognitive Performance Scale [33]; ADL-status will be measured using the ADL Self-performance Hierarchy[34]; ADL dependency will be measured using the Barthel index [35]; and mobility will be measured using a mobility scale developed from MDS items [23]. Agitation will be measured using the Cohen-Mansfield Agitation Index-short form [36,37]. In addition, socio-demographic characteristics will be assessed at baseline, T2 and T3 for all residents participating in the study: age and gender.

### Process evaluation

For conducting the process evaluation, other samples will be recruited in comparison with the effect evaluation. Depending on the study question, residents' relatives, nursing home staff, educators (nurse specialists), nursing home management, and the Netherlands Health Care Inspectorate (IGZ) will be invited to participate in different parts of the process evaluation.

The process evaluation will monitor the content and feasibility of the intervention program. Data regarding the process evaluation will be gathered regarding the eight month period between baseline and T3. First, to investigate the opinion of nursing home staff, the nursing home management and the residents' relatives about EXBELT and the effectiveness of alternative interventions, structured interviews will be used. Second, intervention fidelity, including the dose delivered, and dose received [38], will be obtained by conducting interviews with nursing home staff, nursing home management, educators and consultants. In addition, checklists and observation forms will be used to document fidelity of the intervention across nursing home units assigned to the intervention group. Finally, to examine the influence of the EXBELT on attitudes and opinions regarding restraint use, we will measure attitudes of nursing home staff using the MAQ [25] at baseline, after the education program and at the end of the project.

### Data analysis

Comparability between the intervention and control groups will be assessed at baseline to check for differences between the two groups on socio-demographic characteristics (age and gender). Outcomes at T2 and T3 will be compared between the intervention and control groups by both univariate and multivariate techniques. Data resulting from the effect evaluation will be primarily analyzed according to the intention-to-treat principle, i.e., including all participants with valid data, regardless of whether they remained in the setting which they were measured at baseline. Subsequently, the results of the intention-to-treat analysis will be compared with the results of a per-protocol analysis, to assess whether protocol deviations have caused bias. In all analyses effect estimates will be adjusted for baseline differences. Dropouts and losses-to-follow up will be described. Data resulting from the process evaluation will mainly be analyzed by means of descriptive techniques.

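### Adjustment depends on baseline differences, with comparability checked only on age and gender, so adjustment for baseline belt use is not secured in this non-randomised study

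*Protocol article*

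**What the plan says.** All statements are in the protocol article.

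- **Allocation** (Design and sample): "Since no randomization took place, allocation was based on avoidance of contamination bias". Geography also played a part: "wards from each of the four nursing associations that were situated closely together were allocated to the same group". The sample is "four nursing home associations, 13 nursing homes with a total of 26 psychogeriatric wards".
- **Baseline check** (Data analysis): the groups are compared to "check for differences between the two groups on socio-demographic characteristics (age and gender"). No other characteristic is listed.
- **Contrast** (Data analysis): "Outcomes at T2 and T3 will be compared between the intervention and control groups by both univariate and multivariate techniques". This describes follow-up levels; change from baseline is not mentioned.
- **Adjustment** (Data analysis): "In all analyses effect estimates will be adjusted for baseline differences". No variable is named, and nothing says how a difference is to be established.
- **Primary outcome** (Effect evaluation): "Belt use will be measured at baseline, T2 and T3 using the observation tool".
- **Case mix** (Effect evaluation): data on cognition, ADL and mobility "will be collected only for those residents who are restrained by a belt".

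**The concern.** Allocation gives no assurance that the groups start level, so the primary comparison leans on its baseline adjustment. The usual first covariate is the baseline value of the outcome, which is available here. The only check described omits it, and the adjustment sentence refers to differences without saying which variables are examined. On that wording an analyst could examine age and gender, find them similar, and compare T3 belt use with no account of where each group started.

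Unequal starting levels are plausible. Ward eligibility sets a floor of 10% belt prevalence and no ceiling. The Background cites 10% to 14% for Dutch nursing homes, and the pilot ward had 12 belts in 30 residents.

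A rule driven by observed differences is also weak in itself. An imbalance large enough to distort the result can easily go unflagged at this sample size.

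**Working it through.** **Inputs from the article.** Two-sided alpha 0.05, power 60%, 216 residents per group in the analysis, consent 80%, drop-out 25%, 720 selected, an expected 50% reduction with no change in control (Sample size considerations); cited belt prevalence 10% to 14% (Background).

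**The plan's own figures.** The control rate is not stated. At 14% versus 7% the usual two-proportion formula gives 187.6, so 188 per group. With continuity correction it gives 215.2, so 216, which matches. Selection: 216/0.75 = 288 consented per group, 288/0.80 = 360, and 2 × 360 = 720, which also matches. These figures do not bear on the point; they supply the n used below.

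**Assumptions for the illustration.** Baseline belt use differs between groups within the cited 10% to 14%; each group's level persists apart from any intervention effect; T3 is compared without adjustment for baseline belt use; clustering is ignored.

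**Formula.** With group rates a < b, d = b − a and p the mean of a and b:
- SE0 = sqrt(2p(1−p)/n)
- SE1 = sqrt(a(1−a)/n + b(1−b)/n)
- P(significant, favouring the lower group) = 1 − Φ((1.96·SE0 − d)/SE1)

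**1. No intervention effect, n = 216 per group.**
- 10% vs 14%: SE0 = 0.0313, SE1 = 0.0312, (0.0613 − 0.04)/0.0312 = 0.68, probability 24.8%. The apparent reduction is 1 − 10/14 = 29%.
- 10% vs 12%: SE0 = SE1 = 0.0301, (0.0590 − 0.02)/0.0301 = 1.30, probability 9.7%. The apparent reduction is 1 − 10/12 = 17%.
- The nominal rate in one direction is 2.5%.

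**2. True 50% reduction, n = 216 per group.**

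| Start, intervention | Start, control | T3, intervention | T3, control | Apparent reduction | Power |
|---|---|---|---|---|---|
| 14% | 10% | 7% | 10% | 30% | 20% |
| 10% | 10% | 5% | 10% | 50% | 51% |
| 10% | 14% | 5% | 14% | 64% | 89% |

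**3. Would a baseline test flag the imbalance?** The article names no test; suppose a difference means a significant one. With 288 consented residents per group and 10% vs 14%: SE0 = 0.0271, SE1 = 0.0270, (0.0531 − 0.04)/0.0270 = 0.48, probability 31%. Such a rule would miss this imbalance about two times in three.

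**Effect of ignoring clustering.** The 4-point shift in part 1 and the apparent reductions do not depend on it. The probabilities do. A test that allows for ward clustering has a larger standard error, so it would flag the baseline imbalance less often, and the 24.8% would also fall.

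**The case against.** The strongest reply is that the adjustment sentence covers all analyses and is not limited to age and gender. Belt use is measured at baseline, so a difference in it falls within a plain reading. The age and gender sentence describes a comparability check and is not presented as the covariate list. The phrase could even mean adjustment for baseline values. And a condensed article commonly leaves the exact covariate list to an analysis plan.

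Much of this stands. A reader might infer that baseline belt use is left uncontrolled; the text does not support that, because nothing excludes it. A reader might also infer selection by significance test; no test or threshold is stated, so part 3 of the working is conditional on that reading. An unnamed covariate list alone would not be a finding. What remains is that the article does state a check that omits the primary outcome and an adjustment tied to differences, and neither secures the covariate that matters most.

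A second tempting inference is confounding by association. It is not shown. The allocation sentence can be read as grouping neighbouring wards within each association, so that associations contribute to both groups, and Figure 1 is not available to settle it.

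A third is that the design has no other protection, or no case-mix data at all. The study is longitudinal with a baseline outcome measurement, all wards had to meet the prevalence floor, and psychoactive drug use, falls and other restraints are recorded at baseline with no stated restriction to belted residents. The gap is specific to cognition, ADL and mobility.

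Finally, the likely bias as a share of the effect cannot be derived from the article. It would need an intracluster correlation, a within-resident correlation and a split of wards between groups, none of which is given.

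**Conclusion.** The point holds as a weakness in what is secured: in a non-randomised comparison, the stated check and the difference-dependent rule do not guarantee adjustment for baseline belt use. If it were omitted, a starting imbalance within the article's own cited range could create an apparent 29% reduction from no effect (significant about 25% of the time), or turn a true 50% reduction into an apparent 30% or 64%. These figures assume persistent levels, no baseline adjustment and independent residents. They show what could happen under the wording and do not predict this study's bias. Separately, cognition, ADL and mobility cannot be adjusted for across the whole sample, because residents without a belt have no values. This is a free improvement.

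**What to change.** Replace the adjustment sentence with a fixed covariate set, used whatever the observed balance:

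- the resident's baseline value of the outcome analysed (belt status for the primary outcome), with age and gender;
- association, optionally, as the block within which wards appear to have been allocated;
- for newly admitted residents (research question 2), who have no baseline value, the ward's baseline belt prevalence instead.

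Keep the baseline comparison as description only, add belt use to it, and do not let it choose covariates. State as a limitation that the effect cannot be adjusted for cognition, ADL or mobility across all residents, because those scales are collected only in belted residents. Under Study progress, baseline measurement is complete and implementation has begun, so pre-intervention values of these scales can no longer be gathered for everyone.

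The cost is a few lines of text. The covariates are already collected and analysis is planned for 2010, so the set can be fixed beforehand.
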